### Data management {19}

All data management processes follow a data protection plan developed under the supervision of the Department of Data Protection at the German Cancer Research Center (DKFZ). Data are entered into a secure, password-protected database using pseudonymized participant identifiers. Automated validation rules, range checks, audit trails, and real-time query resolution support data quality. Access rights are role-based and restricted to authorized study staff. Monitoring of data quality is performed by the coordinating center and includes remote and on-site review. Full data management procedures are documented in the trial data management handbook.

### Confidentiality {27}

Personal identifying information is stored separately from clinical study data. Pseudonymization is applied via site-specific alias keys accessible only to authorized investigators. MRI image data are stored securely using the same pseudonymization structure. All paper documents are kept in locked archives at study sites. Data transmission occurs via encrypted channels. Data will be retained for a minimum of 10 years after study completion in accordance with German regulations and GDPR. No personally identifiable data will be disclosed in publications.

### Plans for collection, laboratory evaluation and storage of biological specimens for genetic or molecular analysis in this trial/future use {33}

No biological specimens for genetic or molecular analysis are collected as part of the PRIMA main trial.

## Statistical methods

### Statistical methods for primary and secondary outcomes {20a}

The primary analysis will compare the detection proportion of clinically significant prostate cancer (csPCa; ISUP ≥ 2) between Arm A (TB only) and Arm B (TB + SB) using a non-inferiority framework. Non-inferiority for csPCa detection will be assessed based on the absolute difference in detection proportions (π_TB − π_TB + SB), evaluated using the likelihood score test by Gart and Nam for binomial parameters at a one-sided α level of 0.05. The non-inferiority margin is δ = 13%. Superiority testing for the secondary co-primary endpoint (detection of clinically insignificant PCa, ISUP 1) will be evaluated based on the ratio of detection proportions (π_TB/π_TB + SB) using a one-sided α level of 0.05. All hypothesis tests apply a fixed global significance level of *α* = 0.05.

Secondary outcomes—including biopsy-related complications, biopsy avoidance, diagnostic performance measures, and biopsy approach comparisons—are defined in the Outcomes section according to domain, measurement, metric, method of aggregation, and timepoint. Biopsy-related complications will be summarized as proportions by study arm at 30 days post-procedure. Biopsy avoidance will be reported as the proportion of participants not undergoing biopsy following mpMRI triage at screening. Diagnostic performance outcomes (e.g., DRE, bpMRI vs mpMRI) will be evaluated using standard accuracy measures (e.g., sensitivity, specificity) where applicable.

All detection outcomes are defined as proportions (number of participants with the outcome divided by the number of participants undergoing biopsy in the respective arm). Secondary outcomes will be analyzed descriptively and, where appropriate, using inferential statistical methods.

Patient-reported outcomes (EPIC-26, EORTC-QLQ-C30, VAS) will be analyzed using mixed models for repeated measures (MMRM), including treatment arm, timepoint, and baseline values as covariates.

A detailed statistical analysis plan (SAP) will be finalized and archived prior to database lock and prior to any unblinded analyses.

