#### Sample size

The sample size is derived from the following expected PI-RADS distribution (own institutional data and PRECISION trial data [8, 23]): 25% PI-RADS 1–2, 25% PI-RADS 3 (15% PSAD ≤ 0.15 and 10% PSAD > 0.15), 30% PI-RADS 4, and 20% PI-RADS 5. Thus, the prevalence of PI-RADS 4/5 and PI-RADS 3 PSAD > 0.15 is estimated at 60%. The estimated prevalence of csPCa in this cohort is 50%, and the detection of low-grade PCa (ISUP 1) is expected to be 15%.

Based on prior evidence, targeted biopsy alone is expected to reduce ISUP 1 detection by at least 40% [7], and SB adds approximately 5% absolute incremental csPCa detection according to randomized trials and a Cochrane meta-analysis [9, 10, 13, 14]. Non-inferiority of TB alone compared with TB + SB will be evaluated by testing H0: Δ0 = πTB − πSB + TB ≤ − δNI, with a non-inferiority margin of δNI = 13%. The non-inferiority margin of 13% was chosen based on prior evidence demonstrating an approximate 4–5% incremental detection of clinically significant prostate cancer with systematic biopsy, allowing for a conservative margin that maintains clinical relevance. Assuming πSB + TB = 50% and a true difference of Δ = − 5%, 477 patients per arm ensure 80% power at one-sided α = 0.05.

Superiority in avoiding ISUP 1 diagnoses will be tested under H0: πTB/πSB + TB ≥ 1. With πSB + TB = 15% and a true reduction ratio to 60%, a sample size of 460 patients per arm ensures 88% power at *α* = 0.05.

Therefore, 1590 analyzable patients are required (2 × 477/0.6 = 1590), and accounting for 20% dropout, approximately 1908 must be allocated within 3 years.

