## Assignment of interventions: allocation

### Sequence generation {16a}

Participants will be randomized in a 1:1 allocation ratio to either Arm A (targeted biopsy only) or Arm B (targeted + systematic biopsy). Randomization will use computer-generated permuted blocks of variable size and will be stratified by study center to ensure balance across recruitment sites.

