### Methods in analysis to handle protocol non-adherence and any statistical methods to handle missing data {20c}

The primary analysis will follow the intention-to-treat (ITT) principle, including all randomized participants regardless of protocol deviations. A secondary per-protocol (PP) analysis will exclude patients with major deviations (e.g., incorrect biopsy allocation, inadequate imaging quality). Missing outcome data will be addressed primarily through multiple imputation techniques assuming missing at random. Sensitivity analyses include complete-case analysis and worst-case imputation for key endpoints.

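### The primary csPCa test is stated without centre or PI-RADS, so a valid analysis gives up some precision that baseline adjustment would recover

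*Protocol article*

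**What the plan says.** In section {20a}, "Non-inferiority for csPCa detection will be assessed based on the absolute difference in detection proportions", and that difference is to be "evaluated using the likelihood score test by Gart and Nam for binomial parameters", at one-sided alpha 0.05. The margin is 13 points. Neither a stratum nor a covariate is attached to this test. The same section does list covariates for the patient-reported outcomes.

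Section {16a} says allocation is "stratified by study center to ensure balance across recruitment sites", and section {8} agrees; section {9} lists eight sites. Section {17a} states that PI-RADS is scored before randomization. The randomization scheme in {11a} uses PI-RADS, with PSA density for category 3, to decide who is randomized. Every randomized man therefore has a recorded category.

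Centre appears in no analysis model in the article. Baseline PI-RADS category enters only the exploratory subgroup models in {20b}. On missing outcomes, {20c} says: "Missing outcome data will be addressed primarily through multiple imputation techniques". Section {20a} leaves a detailed statistical analysis plan to be finalized before database lock.

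**The concern.** Suppose csPCa rates differ between PI-RADS 3, 4 and 5, or between centres. A comparison of two crude proportions then carries between-stratum variation in its standard error that an adjusted estimate of the same absolute difference would remove. The confidence limit that is compared with the 13-point margin then lies further from the estimate than it needs to. In a trial planned at 80% power, that precision is available without recruiting anyone further.

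**Working it through.** **Inputs.** From section {14}: TB + SB rate 50%, true difference −5 points (TB 45%), margin 13 points, one-sided alpha 0.05, 80% power, 477 per arm. Among randomized men, PI-RADS 3 : 4 : 5 is 10 : 30 : 20, so the weights are 1/6, 1/2 and 1/3. The csPCa rates by PI-RADS category or by centre are not in the article. They are assumed below and shown as ranges.

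**Step 1: reproduce 477.** The distance from the true difference to the margin is 0.13 − 0.05 = 0.08. The unrestricted variance term is 0.45×0.55 + 0.50×0.50 = 0.4975. Under a true difference of −0.13 the restricted estimates are 0.4105 and 0.5405, giving 0.4105×0.5895 + 0.5405×0.4595 = 0.4904. Then

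n = [(1.645×√0.4904 + 0.842×√0.4975) / 0.08]² = 476.02, rounded up to 477.

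Power at 477 is 80.1% by this formula, and 79.4% by exact binomial enumeration of the score test without skewness correction. The planned number is thus that of a single-table score test with no strata. The simpler unpooled formula gives 481 per arm, and 79.7% power at 477; it is the baseline for the next steps.

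**Step 2: adjust for PI-RADS.** For a stratum-weighted difference the variance term becomes V = Σ w[p_C(1−p_C) + p_T(1−p_T)]. Overall rates are held at 50% and 45%. Power is Φ(0.08×√(477/V) − 1.645).

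| Assumed TB + SB rates, PI-RADS 3/4/5 | V relative to 0.4975 | n per arm for 80% | Power at 477 |
|---|---|---|---|
| No gradient | 1.000 | 481 | 79.7% |
| 41/46/61% | 0.975 | 469 | 80.6% |
| 31/46/66% | 0.939 | 452 | 81.9% |
| 20/42/77% | 0.829 | 399 | 85.9% |
| 16/41/81% | 0.778 | 374 | 87.8% |

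Worked row, 20/42/77% with TB rates 16.4/36.2/72.4%: V = 0.2075 + 0.2049 = 0.4124, and 0.08×√(477/0.4124) − 1.645 = 1.076, so power is 85.9%. The standard error falls from 0.0323 to 0.0294. The distance from the estimate to the one-sided 95% limit falls from 1.645×0.0323 = 5.3 points to 1.645×0.0294 = 4.8 points.

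**Step 3: cross-check by explained variance.** For rates 20/40/75%, the mean is 0.483 and the between-stratum variance 0.0406. R² = 0.0406/(0.483×0.517) = 0.162, effective n = 477/(1 − 0.162) = 569, and power is about 86%. For a flatter 35/47/62%, R² = 0.036 and power is about 81%.

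**Step 4: simulation.** Twenty thousand runs at 477 per arm, with a constant −5-point difference, compared simple unadjusted and PI-RADS-weighted tests of the risk difference. With rates of about 22/41/77.5%, power was 79.3% unadjusted and 86.0% adjusted. With about 30/44/69%, it was 78.9% and 82.4%. At a true difference of −13 points the rejection rate was 0.048 and 0.050 unadjusted, and 0.049 and 0.051 adjusted. The gain is not bought with inflated alpha, and the unadjusted test also holds its level.

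**Step 5: centre alone.** With V = 0.4975 − 2×SD², where SD is the between-centre standard deviation of the csPCa rate:

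| SD (points) | Power at 477 |
|---|---|
| 3 | 79.9% |
| 5 | 80.1% |
| 10 | 81.2% |
| 15 | 83.0% |

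Against 79.7%, that is about 0 to 3 points. It need not add in full to the PI-RADS gain, because centres may differ partly through their PI-RADS mix.

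**The case against.** The strongest reply is that nothing here is wrong. The named test is valid, it matches the sample size calculation, and it meets the stated power. A full analysis plan is still to come and could specify a stratified version; the article never uses the word unstratified. The size of any gain rests on rates the article does not supply, and at the flat end it is under one point.

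Most of this stands and sets the weight of the point. It does not remove it. The article goes beyond leaving the matter open: it fixes test, scale, alpha and margin, and its 477 is the single-table figure. The adjusted estimate answers the same question on the same scale.

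Three stronger readings are tempting, and the documents do not support them:

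- **That the crude test is invalid, or the trial underpowered, because the randomization factor is ignored.** The checks above show the level held and about 80% power.
- **That the gain comes from precision built in by stratification.** Only centre was a stratification factor, and it brings little. PI-RADS is a baseline covariate and accounts for nearly all of the gain.
- **That multiple imputation rules out the score test.** Section {20c} states only a general approach, and pooling details belong in the analysis plan. A stratified score interval would raise the same pooling question, so this is a convenience of the standardized estimate and not a defect of the crude test.

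Whether the 20% loss allowance is large enough is a separate matter and adds no weight here.

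**Conclusion.** The point holds as a recommendation on efficiency. At 477 per arm, PI-RADS adjustment would lift power from about 80% to roughly 81–88%. On the same unpooled formula, that equals a requirement of 374–469 per arm instead of 481. These figures assume the planned 10:30:20 mix, overall rates of 50% and 45%, and the rates by category set out above. If csPCa rates hardly differ by PI-RADS, the gain is negligible. No gain was calculated for PSA density or age, so none is claimed.

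**What to change.** In the analysis plan, before any unblinded analysis, keep the absolute difference, the 13-point margin and one-sided alpha 0.05. Name as primary a standardized (g-computation) risk difference from a logistic model with arm, centre and PI-RADS category (3/4/5). State its standard error method and that estimates are pooled over the multiple imputations by Rubin's rules. Retain the crude Gart-Nam test as a sensitivity analysis.

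The cost is wording and modest programming; the sample size need not change. The section on trial status reports that nobody had been enrolled at submission, so the change can be made cleanly.

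One downside needs a prespecified rule: how small centres are pooled. Fully crossing 8 centres with 3 categories gives 24 cells. With equal centres, PI-RADS 3 would average 477/8/6 ≈ 10 men per centre per arm, or about one ISUP 1 event at rates of 9–15%. Main effects for centre and PI-RADS avoid that crossing, but the pooling rule matters most if the same adjustment is extended to the ISUP 1 ratio.

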### Criteria for discontinuing or modifying allocated interventions {11b}

Because PRIMA is a diagnostic accuracy trial without therapeutic intervention, no modification or dose adjustment of assigned study procedures is possible. However, allocated biopsy procedures may be discontinued or deferred for an individual participant under the following circumstances:Participant decision or withdrawal of consent at any point prior to or during the biopsy procedure, without a requirement to provide justification and without any impact on subsequent clinical care.Medical judgment of the responsible study physician, if performing the biopsy would expose the participant to unacceptable clinical risk (e.g., acute infection, severe bleeding disorder, anticoagulation that cannot be safely paused, or significant deterioration in health status).Safety considerations arising during the procedure, including uncontrolled pain, vasovagal reaction, or procedure-related complications.Protocol deviations mandated by emergency clinical indications, if continuation is deemed inappropriate for patient safety.

Participants who discontinue or do not complete their allocated intervention will be encouraged to remain in the study for follow-up assessments where possible, and data already collected may be included in analyses according to the predefined statistical plan (intention-to-treat principle).

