### Outcomes {12}

#### Co-primary outcomes

Detection of clinically significant prostate cancer (csPCa; ISUP ≥ 2)

Defined as the presence of csPCa on histopathology at initial biopsy (measure: histopathological assessment; metric: binary yes/no). Results will be expressed as the proportion of participants with csPCa in each study arm (method of aggregation: proportion), assessed at index biopsy (timepoint).Detection of clinically insignificant prostate cancer (ISUP 1)

Defined as the presence of ISUP grade group 1 cancer on histopathology at initial biopsy (measure: histopathological assessment; metric: binary yes/no). Results will be expressed as the proportion of participants with ISUP 1 cancer in each study arm, assessed at index biopsy.

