## Assignment of interventions: blinding

### Who will be blinded {17a}

Clinical teams cannot be blinded due to procedural differences between study arms. Radiological assessment (including PI-RADS scoring) is performed prior to randomization and is therefore inherently blinded to treatment allocation. Biostatistical analyses will be conducted on pseudonymized datasets, with treatment allocation unmasked only after database lock, following finalization of the statistical analysis plan.

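### Detection proportions, including both co-primaries, are defined over biopsied men, while the primary analysis is ITT on all randomized men with imputation; the two rules need reconciling

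*Protocol article*

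**What the plan says.** Two sections of the protocol article set the population for the primary comparison.

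- **Statistical methods {20a}.** All detection outcomes are proportions, each being the "number of participants with the outcome divided by the number of participants undergoing biopsy in the respective arm". The sentence makes no exception for the co-primary endpoints.
- **Non-adherence and missing data {20c}.** "The primary analysis will follow the intention-to-treat (ITT) principle, including all randomized participants regardless of protocol deviations". On missing data: "Missing outcome data will be addressed primarily through multiple imputation techniques assuming missing at random". And further: "Sensitivity analyses include complete-case analysis and worst-case imputation for key endpoints".

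Two other sections bear on which rule is meant.

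- **Co-primary outcomes {12}.** The endpoint is histopathology at the index biopsy. "Results will be expressed as the proportion of participants with csPCa in each study arm", with no restriction to biopsied men.
- **Discontinuing allocated interventions {11b}.** The plan foresees randomized men whose biopsy is not done or not completed, for example through "Participant decision or withdrawal of consent at any point prior to or during the biopsy procedure", and also for medical or safety reasons. It refers the data of such men to the intention-to-treat principle.

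On blinding, {17a} states: "Clinical teams cannot be blinded due to procedural differences between study arms".

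**The concern.** The primary outcome exists only if the index biopsy is done. A randomized man without that biopsy is therefore the main kind of man with a missing primary outcome. Section {20a} removes him from the denominator, while {20c} keeps him and imputes his result. Under {20a} the planned imputation has almost nobody to act on, and the complete-case analysis, listed in {20c} as a sensitivity analysis, becomes the primary one.

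Whether a man is biopsied is settled after randomization. Clinical teams know the allocation, and Arm B adds a 12-core systematic biopsy to the targeted cores, so refusal or deferral could plausibly differ between arms. If non-biopsy is also related to whether csPCa would have been found, the biopsied men in the two arms are no longer comparable. The non-inferiority conclusion could then be wrong in either direction.

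**Working it through.** **1. The plan's own figure.** Inputs from Sample size {14}: 50% csPCa with TB + SB, true difference -5 points (so 45% with TB), margin 13 points, one-sided α = 0.05, 477 per arm. For the score test, power is

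Φ{[(p_A − p_B) + 0.13 − 1.645·SE0] / SE1},

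where SE1 uses the true rates and SE0 the rates fitted under a difference of exactly -13 points. The fitted rates are 41.05% and 54.05%, so SE0 = 0.03206 and SE1 = 0.03230. Then (0.08 − 1.645 × 0.03206) / 0.03230 = 0.844, and power is 80.1%. At 476 per arm it is just under 80%. The planned 477 reproduces.

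**2. When the two denominators coincide.** If u_A and u_B are the fractions of randomized men not biopsied, {20a} divides by n(1 − u) and {20c} by n. They are equal only when u_A = u_B = 0. The documents give no value for either fraction, so everything below is an assumption, shown as a range.

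**3. The arithmetic of selection.** If the rate that would have been found among all randomized men is p, and among unbiopsied men q, the biopsied-only rate is (p − u·q) / (1 − u). Except where stated, the number randomized per arm is 1908 × 0.6 / 2 = 572.

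**4. Random non-biopsy (q = p).** The biopsied-only difference stays at -5 points. Power is 0.86 with no non-biopsy, 0.835 with 5% in A and 10% in B, and 0.786 with 20% in both. Only precision is lost.

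**5. Selective non-biopsy, true difference -5 (45% vs 50%).** Assume 10% unbiopsied in A with q = 27%, and 20% in B with q = 30%.

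- A: (0.45 − 0.10 × 0.27) / 0.90 = 0.47
- B: (0.50 − 0.20 × 0.30) / 0.80 = 0.55

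The apparent difference is -8 points. Power is 46.6% at 477 per arm and about 47% with the 515 and 458 men who would be biopsied out of 572. This error works against TB alone.

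**6. Selective non-biopsy, truth at the margin (37% vs 50%).** The probability of concluding non-inferiority should be 0.05.

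| Unbiopsied A / B | q in A / B | Biopsied-only A vs B | Difference | P(non-inferior) |
|---|---|---|---|---|
| none | – | 37.0% vs 50.0% | -13.0 | 0.05 |
| 5% / 5% | 25% / 25% | 37.6% vs 51.3% | -13.7 | 0.03 |
| 5% / 10% | 25% / 60% | 37.6% vs 48.9% | -11.3 | 0.14 |
| 5% / 15% | 37% / 70% | 37.0% vs 46.5% | -9.5 | 0.31 |

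The last two rows favour TB alone. Both need the unbiopsied men in Arm B to be at clearly higher risk than those in Arm A.

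**The case against.** The strongest reply is that {20a} contains one loose parenthesis. Around 40% of enrolled men are triaged out by MRI, so the phrase may only be meant to separate the biopsy population from the larger enrolled cohort. Sections {11b}, {12} and {20c} all point to ITT. That is a fair guess at the intent, and it supports the direction of the fix. It does not remove the conflict, because the sentence defines the denominator within each arm, and men triaged out by MRI are never in an arm.

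A second reply also has force. Multiple imputation under missing-at-random, done within arm without informative covariates, gives essentially the biopsied-only estimate, so changing the denominator alone would leave the -8 points of step 5 in place. Imputation recovers only the selection that its predictors explain. The fix must therefore name predictors.

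A reader might also infer several stronger points that the documents do not support:

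- **That randomization is broken.** Bias needs non-biopsy to be related to would-be detection, and its extent or pattern to differ by arm. Step 4 shows no bias otherwise.
- **That the denominator could be chosen after seeing the results.** Sections {17a} and {20a} require the SAP to be final before database lock and before any unblinded analysis, with allocation unmasked only after lock.
- **That 20% of randomized men will lack a biopsy.** The 20% loss applies to all 1908 enrolled men, MRI-negative men included, and is not tied to the interval between randomization and biopsy.
- **That counting unbiopsied men as not detected measures the size of the conflict.** Neither section states that rule.
- **That the secondary place of the per-protocol analysis is an error.** The plan says "A secondary per-protocol (PP) analysis will exclude patients with major deviations". Requiring ITT and per-protocol results to agree is a convention, and the arm-wise definition of the worst case is detail for the SAP.

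**Conclusion.** The published text gives two incompatible populations for both co-primary endpoints. Followed literally, {20a} makes a complete-case analysis primary, contrary to {20c}, and conditions the comparison on a post-randomization event in an unblinded trial. The contradiction rests on the wording alone and needs no assumption.

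The size of any bias does rest on assumptions, because non-biopsy rates and the risk of unbiopsied men are not given. Within the range tried, the effect runs from none (random non-biopsy), through an apparent -8 points for a true -5 with power near 47%, to a false non-inferiority probability of 0.14 to 0.31 against 0.05. Since the primary endpoint is affected and the direction cannot be predicted, the wording should be settled before recruitment produces data.

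**What to change.** In {20a}, replace the denominator with *all participants randomized to the respective arm*. State that men without an index biopsy are handled by the multiple imputation already named in {20c}, using baseline predictors already collected, such as PI-RADS category, PSA density, age and center, so that it can recover the selection these explain. Keep the biopsied-only proportion as the complete-case sensitivity analysis that {20c} already lists.

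The cost is a short change to the protocol, carried into the SAP, and slightly more analysis work. The 477 per arm stays as planned. The article reports that nobody had been enrolled when it was submitted.
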